## Abstract

Intimate partner violence (IPV) during pregnancy, a condition as common as obstetrics conditions like gestational diabetes, is associated with maternal and neonatal complications. Systematic detection of IPV is not well established in antenatal screening probably because the effectiveness of protective interventions has not been evaluated. E-health interventions may be beneficial among mothers exposed to IPV. Prior to performing a full-scale effectiveness trial for such an intervention, a pilot study is required to assess the feasibility of randomising a sufficiently large number of women exposed to IPV during pregnancy. The eIPV trial is a randomised pilot study nested within a cohort of consenting mothers who screen positive for IPV in the first antenatal visit at <12 weeks’ gestation and accept an e-health package (psychological counselling by videoconference) in Spain and Denmark. Twenty eligible mothers from the above cohort will be randomised to either intervention or control. The intervention group will receive the e-health package as part of the cohort. The control group will be invited to accept a delay in the intervention (e-health package eight weeks later). After consenting to delay, the control group will provide comparative data without losing the opportunity of obtaining the intervention. We will determine estimates of rates of informed consent to randomization, and the rates of adherence and dropout following randomization. Qualitative interviews will be conducted to examine the women’s perception about the benefit of the intervention, reasons for acceptability and non-adherence, and obstacles to recruitment, randomisation and consent. The results will inform the trial feasibility and variance of key clinical outcome measures for estimation of sample size of the full-scale effectiveness trial.

## Introduction

### Background and rationale

Intimate partner violence (IPV) is one of the most common forms of violence against women and includes physical, sexual, and emotional abuse and controlling behaviour [1]. Globally, the lifetime prevalence of physical and sexual IPV for women is around 30% [2, 3]. Violence during pregnancy is more common than preeclampsia or gestational diabetes which are routinely screened for antenatally [4, 5]. In Spain, 3.6% of pregnant women have suffered physical IPV during pregnancy [6, 7]. In Denmark, 2.5% of pregnant women have reported physical violence [8]. Although the true prevalence of IPV during pregnancy in EU is unclear, it is evident that a substantial minority of women experience violence during pregnancy [9]. Moreover, pregnancy violence often continues into the postpartum period with an estimated 10% of hospitalizations due to injury in pregnancy are the result of intentional injuries inflicted upon the pregnant woman [10]. Also, IPV during pregnancy has been linked to depression, both during pregnancy and in the postpartum period [11].

To improve the health of pregnant women and their infants, it is important that targeted IPV interventions are developed and implemented as part of routine antenatal care.

E-health tools are potential solutions to deliver effective treatment and support to women exposed to IPV. eHealth interventions have the potential to provide more flexibility and safer spaces than face-to-face interventions, making it particularly useful for screening violence, empowering women and reducing exposure to IPV [12]. IPV survivors considered appropriate and necessary to be screened using eHealth strategies in antenatal care settings and perceived that video counselling is a viable and acceptable tool for pregnant women who experience IPV [13]. Trials have shown that e-health screening tools are effective in getting women to disclose or detect IPV [14–16]. Trials have also found that women who receive telephone counselling combined with other forms of support or a web-based safety decision aid kit are more likely to adopt safety behaviours than women in a control group, which were not offered e-health solutions [17–20]. It has been found that online safety planning is a feasible method among pregnant women [21].

Based on the available evidence, we have developed an e-health intervention package combining an online screening tool and video counselling sessions by trained providers for pregnant women who screen positive for IPV. Screening for IPV combined with an empowerment intervention that includes brief education and video counselling on safety planning may have potential to address repeated IPV and associated adverse health effects among pregnant women. However, prior to performing a large interventional trial, a pilot study is needed to identify barriers to recruitment, assess feasibility and acceptability of the treatment, and fine-tune study procedures.

### Objective

The objective is to assess the need and feasibility of randomising a sufficiently large number of women exposed to IPV during pregnancy in a full-scale future randomised trial. To achieve this, we will:

estimate rates of consent to randomization, and the rates of adherence and dropout following randomization (for the use in sample size estimation)determine recruitment durationexamine the women’s perception about the benefit of the interventiondetermine the reasons for acceptability, non-adherence, and obstacles to recruitment, randomisation and consent through qualitative interviews

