**Fig 2 pone.0282997.g002:**
[figure not shown]
Flowchart of eIPV trial.

In the second stage, participants who have been assigned to the control, will be reapproached and given information about their participation in the control group. At this stage, they will be invited to accept a delay in the intervention (e-health package eight weeks later) and be asked to give the second informed consent for a delayed intervention. Those who decline will remain in the cohort study. Those in the cohort only group will not be informed about the randomization, as their subsequent follow up in the study will remain part of the cohort study to which they would already have consented in the first stage. We will substitute the women who not consent being part of the control until we reach the sample required (5 women in each country). This information will be also analysed for a future full-scale RCT.

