### Eligibility criteria

All women who fulfil the inclusion criteria will be screened and invited to receive an e-health package. Of those who accept the e-health intervention, 20 women will be randomised, 10 women in each country. In Spain and Denmark, respectively, 5 will be allocated in the intervention group and 5 will be asked to consent to be in the control group.

Inclusion criteria: pregnant women at <12 weeks gestation, who screen positive in IPV at the first antenatal visit and accept the e-health package.

Exclusion criteria: (1) women who cannot be informed about the study without their partners or other family members knowing; (2) mentally or physically incapacity to participate in the study; (3) women below 16 years in Spain or below 18 years in Denmark; (4) inability to understand Danish/Spanish, (5) lack of internet and electronic device and (6) women with extreme severity of IPV. Women selected to participate in the trial in this situation will receive an evaluation of danger before randomisation. If the severity of IPV is confirmed to be at high level of danger, these pregnant women will be routinely treated and supported according to the standard protocol in each country. Following this path, any potential risk for the women will be taken into account from the beginning of the process and women will be protected. Women who have same-sex partners will be screened, but their data will not be used for the purpose of this study.

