#### Progression criteria

Table 1 outlines the main criteria that will be considered to assess the feasibility of a full-scale RCT. In addition, our qualitative findings will also be used to support the decision-making around progression to a full-scale trial. For example, if a progression criterion outlined in Table 1 does not meet the threshold for progression, but we have developed a qualitative understanding of why this occurred and how it could be improved, then it may still be possible to proceed with the full trial. The research team of the STOP project will have access to these interim results.

**Table 1 pone.0282997.t001:** Suggested progression criteria in eIPV trial.

Feasibility objectives and related data to be collected	Go criteria to proceed to full trial	Criteria to reassess and adjust full trial protocol	Stop criteria
Study population			
1. Consent rate of eligible women	Rate >25% of eligible women agreeing to participate.	Rate between 11% and 24% women agreeing to participate	Rate <10% of eligible women agreeing to participate
Study outcomes			
2. Proportion of women in either intervention or control group for whom the allocated treatment is adhered to.	Adherence to allocated treatment in >80% of study sample.	Adherence to allocated treatment in between 51% and 79% of study sample.	Adherence to allocated treatment in <50% of study sample.
RCT process			
3. Collection of data on clinical outcomes	Complete data available of >80% of study sample.	Missing data between 21% and 49% of study sample.	Data missing of >50% of study sample.

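### The 20 women said to be randomised are the sample left after control decliners are replaced, so control-arm adherence and dropout after randomisation will most naturally be conditional on second consent

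*Protocol article*

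**What the plan says.** All references are to the protocol article.

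- **Number randomised.** Eligibility criteria: "Of those who accept the e-health intervention, 20 women will be randomised, 10 women in each country". The Abstract gives the same total, and the split is five intervention and five control in each country.
- **Order of events.** Under Trial design (second stage, after Fig 2), randomisation comes first. Then "participants who have been assigned to the control, will be reapproached and given information about their participation in the control group", and these women are asked to consent to an eight-week delay. The intervention group has no second consent.
- **Decliners.** "Those who decline will remain in the cohort study". The replacement rule follows: "We will substitute the women who not consent being part of the control until we reach the sample required (5 women in each country"). The next sentence says: "This information will be also analysed for a future full-scale RCT".
- **Allocation.** Randomisation procedures gives a 1:1 ratio. It does not say whether a substitute is randomised afresh or placed directly in control.
- **Purpose of the rates.** One Objective bullet lists the rate of consent to randomisation together with "the rates of adherence and dropout following randomization (for the use in sample size estimation").
- **Adherence measure.** Table 1, criterion 2: "Proportion of women in either intervention or control group for whom the allocated treatment is adhered to". Go is above 80% of the study sample, reassess is 51% to 79%, and stop is below 50%. The study sample is not defined there. The secondary outcome on recruitment duration describes the pilot sample as five plus five women per country.
- **Refusal.** The primary outcome is the rate of consent to the control group, and the Statistical analysis section gives it a 95% confidence interval.

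**The concern.** In this modified Zelen design, refusing the delay is an event after randomisation. A woman who declines has been allocated to control and does not follow that allocation. She goes back to the cohort, which receives the package. The Discussion names reluctance to accept the control group, and dropout after allocation to it, as the difficulty the pilot is meant to address.

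Replacing decliners has two effects. First, the stated number randomised is right only if nobody declines. Second, if control-arm adherence and dropout are computed on the five plus five retained women per country, they are conditional on second consent and do not describe everyone randomised. They would still be labelled as rates following randomisation and carried into the full trial's sample size. Criterion 2 could then read Go when the same rate over all randomised women would not.

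**Working it through.** **The plan's own figure.** 2 countries × (5 + 5) = 20. This reproduces, but it is the sample after substitution.

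**Inputs.** Ten consenting controls are needed (5 × 2, Trial design). Let p be the proportion of women allocated to control who accept the delay. The protocol gives no value for p, so a range is shown. To isolate the effect of the denominator, assume that every woman except decliners adheres. On average 10/p women must be allocated to control to obtain ten acceptors. What happens in the intervention arm depends on how substitutes are allocated, which is not stated, so there are two readings.

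- *Substitutes go straight to control.* Randomised = 10 + 10/p. Adhering = 10 + 10 = 20. Adherence over all randomised = 20/(10 + 10/p).
- *Substitutes are randomised 1:1.* About 10/p enter each arm, so randomised = 20/p. Adhering = 10/p + 10. Adherence over all randomised = (10/p + 10)/(20/p) = (1 + p)/2. On this reading the intervention arm also exceeds five per country.

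| p (assumed) | Randomised, straight to control | Adherence | Randomised, 1:1 | Adherence |
|---|---|---|---|---|
| 1.00 | 20 | 100% | 20 | 100% |
| 0.80 | 22.5 | 89% | 25 | 90% |
| 0.67 | 25 | 80% | 30 | 83% |
| 0.60 | 26.7 | 75% | 33.3 | 80% |
| 0.50 | 30 | 67% | 40 | 75% |
| 0.33 | 40 | 50% | 60 | 67% |
| 0.25 | 50 | 40% | 80 | 62.5% |

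Counts are expectations, and the percentages are ratios of expectations.

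**Criterion 2 among retained women.** Under the same assumption it is 100% at every p. For 20/20 the Clopper-Pearson 95% interval is 83% to 100%.

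**Where the Go line is crossed.** Straight to control: 20/(10 + 10/p) = 0.80 gives 10/p = 15, so p = 0.67. With 1:1: (1 + p)/2 = 0.80 gives p = 0.60. Below these values the all-randomised rate is no longer Go.

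**By arm.** Over all women allocated to control, adherence is 10/(10/p) = p, whichever way substitutes are allocated. At p = 0.5 it is 10/20 = 50% (95% interval 27% to 73%), against 100% in the intervention arm. The by-arm rate therefore does not depend on the substitution rule, but the pooled rate does.

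**Full-trial sample size.** Suppose the full trial is analysed as randomised and decliners obtain the full effect of the immediate package (both assumptions). A fraction 1 − p of the control arm then behaves like the intervention arm, the difference between arms shrinks by the factor p, and the required size grows by 1/p²: 1/0.8² = 1.56 at p = 0.8 and 1/0.5² = 4 at p = 0.5. If decliners gain less than the full effect, the factor is smaller.

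**The case against.** The strongest reply is that refusal is not lost. Control consent is the primary outcome, has a confidence interval, and stands in the same Objective bullet as adherence and dropout. The protocol also says that the information on decliners will be analysed. A planner could combine acceptance with adherence among acceptors, and reporting the two separately is a defensible choice. The criteria are called suggested and can be overridden by qualitative findings. Detailed denominators may be in an analysis plan that is not shown. All of this stands, and it limits the severity. It does not reconcile 20 randomised with the replacement rule, and the protocol does not say how the two rates are to be combined.

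The exclusion of decliners from criterion 2 is also an inference. No sentence says they are left out. It is a strong inference, because the pilot sample is described as the five plus five set, and controls who leave the delay later also have their data moved to the cohort.

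A reader might infer more than the document supports:

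- *That the rates describe acceptors only in both arms.* Intervention women give no second consent, so all of them count.
- *That the full trial will be too small whatever its design.* If it replaced decliners, the problem would be selection: consenting controls compared with an unselected intervention arm. No 1/p² deficit follows from that. Even when analysed as randomised, the deficit arises only if the planner ignores the pilot's primary outcome.
- *That criterion 2 would really be Stop.* This needs p below 0.33 with substitutes going straight to control. With 1:1 substitutes and full adherence otherwise, (1 + p)/2 never falls below 50%.
- *That Table 1 shows Go on criteria 1 and 2 while most randomised women do not follow allocation.* This also requires criterion 1 to mean control consent, whereas its wording concerns eligible women agreeing to participate.

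**Conclusion.** The point holds in a limited form and should be fixed. The Abstract and Eligibility criteria give 20 as the number randomised, which agrees with the replacement rule only if nobody declines. Otherwise the number is about 10 + 10/p or 20/p: 30 or 40 women at p = 0.5. Under that rule, control-arm adherence and dropout will most naturally be conditional on second consent, which does not match their description in the Objective section.

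The choice of denominator can change a progression decision. With full adherence among all but decliners, criterion 2 falls from 100% to 67% or 75% at p = 0.5, which is reassess on either reading. It leaves Go once p is no more than 0.67 or 0.60 respectively. These figures rest on assumed values of p and, for the pooled rate, on a substitution rule that the protocol does not state.

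**What to change.** 1. In the Abstract and Eligibility criteria, state that 20 is the retained sample, and that every woman randomised, including control decliners, will be counted and reported.
2. Under Trial design or Randomisation procedures, state how substitutes are allocated (straight to control or 1:1), and reconcile this with the 1:1 ratio and the five per arm per country.
3. Report adherence and dropout by arm over all women randomised, counting decliners as not adhering to allocation, beside the rate among women who gave second consent. Define the study sample in Table 1 and say which rate criterion 2 uses.
4. In the Objective section, state that control acceptance p enters the full trial's sample size as control-arm crossover if that trial is analysed as randomised. The inflation is up to 1/p², with the upper value assuming that decliners get the full immediate effect.

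The cost is mainly wording in these places. No additional participants are needed, because decliners remain in the cohort. Reported adherence will look less favourable whenever women decline.

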### Trial design

A pilot randomised controlled trial (RCT), co-designed by patient input using Zelen’s design with additional qualitative evaluation, will be nested within a cohort study. To write the present protocol, the SPIRIT guidelines were followed (S1 and S2 Checklists).

We will use a modified Zelen’ design with a double consent process [22–24] and a delayed intervention for the control group. In the first stage, informed consent will be sought from all pregnant women to enter a cohort study. A predetermined small number of the cohort will then be randomized, without their knowledge, to intervention or control (to see the SPIRIT schedule of enrolment, interventions and assessments in eIPV trial see Fig 1 and the Flowchart of eIPV trial in Fig 2). The intervention group will receive the e-health package as part of the cohort.

**Fig 1 pone.0282997.g001:**
[figure not shown]
SPIRIT schedule of enrolment, interventions and assessments in eIPV trial.

**Fig 2 pone.0282997.g002:**
[figure not shown]
Flowchart of eIPV trial.

In the second stage, participants who have been assigned to the control, will be reapproached and given information about their participation in the control group. At this stage, they will be invited to accept a delay in the intervention (e-health package eight weeks later) and be asked to give the second informed consent for a delayed intervention. Those who decline will remain in the cohort study. Those in the cohort only group will not be informed about the randomization, as their subsequent follow up in the study will remain part of the cohort study to which they would already have consented in the first stage. We will substitute the women who not consent being part of the control until we reach the sample required (5 women in each country). This information will be also analysed for a future full-scale RCT.

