### Randomisation procedures

The research team will consult the data server on a daily basis to identify women who screen positive in IPV and accept to receive the e-health package to randomly allocate them (using a computer-generated random numbers) in the intervention or control group through randomisation at a ratio of 1:1. IPV counsellors will be informed of the assignments to each group. Women in the intervention group will be blinded but not women in the control group.

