
We will monitor if participants adhere to all the sessions offered for counselling and in case of non-adherence or failure to engage in counselling, the counsellor will follow specific protocol to encourage reengagement. In Spain, the psychologist will contact the woman two to three times through the preferred mean (email or phone). In Denmark, a project midwife will try to contact the woman on the preferred mean (email or phone) at 3 occasions within 6 weeks. The content of the six individually tailored sessions will be based on the Dutton’s Empowerment Model [27] and the Psychosocial Readiness Model [28]. Specifically, the contents will include (session 1) the evaluation of abusive behaviour (which will also served to protect the pregnant women is the level of violence detected is high); (session 2) safety planning, network and resources; (session 3) psycho-education (healthy relationships, cycle of violence…); (session 4) self-esteem and self-care and (sessions 5 & 6) empowerment, choice making and problem solving. The video consultations will be planned for every 2 weeks at a time where the women feel comfortable. However, schedule flexibility will always prevail to promote women participation. Criteria for discontinuing or modifying allocated interventions will be applied to women with an elevated risk for IPV who will be routinely treated according to the standard protocol in each country. In other words, if during the interventions the health providers detect an increased on the level of violence, they will apply the established national protocols to protect the pregnant women.

Control group: IPV positive women who accept the e-Health intervention package will be asked for a second consent to receive a delayed intervention (8 weeks later) and to complete the baseline and outcome measurements. Women can request to leave the control group at any time and receive the intervention immediately (in which case the data will be part of the cohort study).

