Relevant concomitant care and interventions that are permitted during the trial: Women in both the intervention and control groups would be able to benefit from the standard care available for women exposed to IPV thorough the usual provision made by social and health services at any time during the study, if necessary. Indeed, one of the video-counselling sessions will be dedicated to inform women about the available resources in their community. IPV counsellors will specify if women in the intervention and the control group are in need of these resources during the time of the pilot as a valuable information for the future full-scale trial.

To accomplish the objectives, we will collect the following information:

Primary outcome:

Number of IPV positive women, who consented to receive e-health package and consented to randomization in the control group computed as a rate.

Secondary outcomes:

Number of women who consented to receive e-health package computed as a rate.Number of women in the intervention group where complete outcome data were obtained computed as a rate.Number of women in the control group where complete outcome data were obtained computed as a rate.Number of women where there was a study protocol violation computed as a rate.Recruitment duration (in days) to get the pilot sample (5 women for the intervention group and 5 women for the control group, in each country).Benefit of the intervention perceived by women through the information obtained in qualitative interviews.Perception about the duration of delay (the duration in the future full-scale trial will be determine according to the observations derived of the pilot study and the information provided in the qualitative interviews).Reasons for acceptability, non-adherence, and obstacles to recruitment, randomisation, consent and follow-up (through qualitative interviews).

Participant timeline

The participant timeline is illustrated in Fig 1.

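### Replacing controls who decline the delay contradicts the stated 20 randomised, and leaves a control arm, and Table 1 rates, that describe only women willing to wait

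*Protocol article*

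**What the plan says.** All references are to the protocol article.

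- **Number randomised.** The Abstract says "Twenty eligible mothers from the above cohort will be randomised to either intervention or control". Eligibility criteria says "Of those who accept the e-health intervention, 20 women will be randomised, 10 women in each country" and, for each country, "5 will be allocated in the intervention group and 5 will be asked to consent to be in the control group".
- **Allocation.** Under Randomisation procedures, women who screen positive and accept the package are identified daily and placed "in the intervention or control group through randomisation at a ratio of 1:1".
- **Refusal.** In the second stage of Trial design (text after Fig 2), women assigned to control are asked for a second consent to an eight-week delay. "Those who decline will remain in the cohort study". Then: "We will substitute the women who not consent being part of the control until we reach the sample required (5 women in each country". The same paragraph says this information will also be analysed.
- **Later departure.** Under Study interventions and assessments, a control may leave at any time to receive the package at once, "in which case the data will be part of the cohort study".
- **Intervention arm.** These women are not told of the randomisation and get no second consent request.
- **Use of the rates.** The primary outcome is the rate of consent to control. Table 1 sets go, reassess and stop limits for consent (above 25%, 11% to 24%, below 10%), for adherence to allocated treatment in the study sample (above 80%, 51% to 79%, below 50%), and for data completeness. The Abstract and Discussion also say the pilot will inform outcome variance for the full trial's sample size.

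**The concern.** Eligibility criteria fixes how many women are asked. Trial design fixes how many accept. Only one of these can be fixed once a woman says no, and the protocol expects refusals: it plans for substitution, and the Discussion gives reluctance to enter a control group as the reason for the design.

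The removals are also one-sided. A woman who declines or leaves control drops out of the pilot comparison, while an intervention woman has no equivalent exit. Yet refusal of the control allocation is the very failure the pilot is meant to measure. If decliners are replaced before adherence and completeness are computed, refusal shows up in the consent rate but disappears from Table 1 criteria 2 and 3. A full trial analysed as randomised would have to carry those women. The control-arm variance passed to its sample size would likewise come from acceptors only.

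**Working it through.** **1. The plan's own figure.** 2 countries × (5 + 5) = 20. This reproduces, but the control half counts acceptances, not women allocated to control.

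**2. When 20 can hold.** Let p be the probability of accepting the delay. The documents give no value, so a range is shown. Using 25% borrows the go limit in Table 1 as a planning value. The probability that the first ten women asked all accept is p^10: 0.35 at p = 0.90, 0.056 at 0.75, 0.001 at 0.50 and about 1 in a million at 0.25.

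**3. Expected numbers allocated.** Asking until five accept is negative binomial sampling, so the expected number allocated to control is 5/p per country. The text does not say how a substitute is found, so there are two readings:

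- A, only control places refilled: total = 2 × (5 + 5/p)
- B, 1:1 allocation continues: total = 2 × (2 × 5/p)

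**4. Ceiling on Table 1 criterion 2.** Assume that every intervention woman and every accepting control adheres perfectly, and count all allocated women at these expected numbers. Adherent women are then 10 + 10 under A, and 10/p + 10 under B.

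| p | Allocated to control | Total A | Total B | Ceiling A | Ceiling B |
|---|---|---|---|---|---|
| 1.00 | 10 | 20 | 20 | 100% | 100% |
| 0.50 | 20 | 30 | 40 | 20/30 = 67% | 30/40 = 75% |
| 0.25 | 40 | 50 | 80 | 20/50 = 40% | 50/80 = 62.5% |

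With decliners replaced, the ceiling is 100% in every row. At p = 0.25 the same conduct could be scored go with decliners removed, stop under A, or reassess under B. At p = 0.50 both all-allocated ceilings fall in the reassess band. At p = 0.25 the number allocated to control per country has a 95% range of 8 to 38 around its mean of 20.

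**5. Consent percentage under this stopping rule.** With r acceptances among N women asked, r/N overestimates p when sampling stops at r. Summing over the negative binomial distribution:

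| True p | Mean of 5/N (one country) | Mean of 10/N (pooled, same p in both) |
|---|---|---|
| 0.10 | 12.1% | 11.0% |
| 0.25 | 29.1% | 27.0% |
| 0.50 | 54.9% | 52.5% |

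The estimator (r − 1)/(N − 1) averages exactly p in each case. For 10 acceptances among 40 women it gives 9/39 = 23.1%, against a plain 25%.

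**The case against.** **No treatment effect is planned.** The Discussion disclaims effect sizes, and the sample size section says the pilot is not powered for clinical differences. This stands: imbalance between the arms damages no planned comparison. It does not rescue adherence, completeness or variance, which are pilot outputs in their own right.

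**Refusals will be analysed, and refusal is the primary outcome.** This also stands. The consent rate can be estimated if every woman asked is in its denominator. It does not return decliners to the denominators of criteria 2 and 3.

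**The inverse-sampling bias is small.** Largely true. The pooled bias at 25% is two percentage points, while the exact 95% binomial interval for 10 of 40 runs from 12.7% to 41.2%. The Statistical analysis section names no interval method. The ordinary exact binomial interval still covers at least 96% under this stopping rule at p = 0.10, 0.25 and 0.50. Progression also allows qualitative judgement. The bias matters only near a cut-off.

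**25% may be the wrong rate.** Table 1 refers to eligible women agreeing to participate, which need not be acceptance of the delay among women who already want the package. Correct, hence the range above.

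**Stronger readings the text does not support.** A reader might infer that substitutes are put straight into control once the intervention places fill, so that the control arm is mostly unrandomised, recruited later, and the recruitment duration is misleading. No section says so. Randomisation procedures describes continuing 1:1 allocation, under which every substitute would have been randomised. Recruitment duration is defined as the days needed to fill the pilot sample, and it measures that. Nor do the documents give any basis for putting a number on how accepting controls differ clinically from decliners.

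**Conclusion.** The concern holds in a limited form.

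- The 20 randomised and the substitution rule conflict as soon as one woman declines. At 25% acceptance the expected total is about 50 or about 80, depending on an unstated mechanism. A total of 20 at 1:1 remains possible if all ten women first asked accept. Under continued randomisation the 1:1 ratio survives, and what fails is the total of 20 and the five intervention women per country.
- Control adherence, data completeness and outcome variance describe women willing to wait. At 25% acceptance the adherence ceiling falls from 100% to about 40% or 62.5% when all allocated women are counted, which moves it across Table 1 bands. This takes the study sample in Table 1, which is not defined, to mean the 20 women left after substitution.
- The upward bias in the plain consent percentage is real but secondary.

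The sizes rest on an assumed acceptance probability, the same in both countries and constant over time, and the ceilings are evaluated at expected counts.

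**What to change.** 1. **Restate the number.** Describe 20 as the target of five accepting controls plus five intervention women per country, with the number randomised variable. Align the Abstract, Eligibility criteria and Trial design.
2. **State how substitutes arise.** Say that they come only from continued 1:1 randomisation as in Randomisation procedures. Reconcile this with five intervention women per country, since that arm will then exceed five whenever controls decline (about 20 per country expected at 25% acceptance).
3. **Report by allocated arm.** Give adherence and data completeness with all allocated women in the denominators, decliners and leavers included, using their cohort questionnaires. Show the figures for accepting controls alongside, and say which set Table 1 is judged on. Label the variance estimate with the group it comes from.
4. **Consent rate.** Use all women asked to accept control as the denominator. Estimate by (r − 1)/(N − 1), per country with r = 5 and pooled with r = 10 if the rates are similar, with an exact interval matched to the stopping rule.

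**Cost.** The number randomised becomes larger and variable, and adherence will look less favourable. A formal amendment with ethics approval in each country is needed, including confirmation that first-stage consent covers reporting decliners' cohort data by allocated arm. No extra visits or questionnaires are required, because these women remain in the cohort.
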